## Abstract

**Background:**

Nonattendance at scheduled appointments in public hospitals presents a challenge for efficient resource use and may ultimately affect health outcomes due to longer waiting times. Seven percent of all scheduled outpatient appointments in the United Kingdom are estimated to be nonattended. Various reminder systems have been shown to moderately reduce nonattendance, although the effect of issuing fines for nonattendance has not yet been tested in a randomized context. However, such use of financial incentives could impact access to care differently across the different socioeconomic groups. The aim of this study is to assess the effect of fines on hospital outpatient nonattendance.

**Methods/design:**

A 1:1 randomized controlled trial of scheduled outpatient appointments was used, with follow-ups until the date of appointment. The setting is an orthopedic clinic at a regional hospital in Denmark. Appointments for users who are scheduled for diagnostics, treatment, surgery, or follow-ups were included from May 2015 to November 2015. Appointments assigned to the intervention arm include an attachment of the appointment letter explaining that a fine will be issued in the case of nonattendance without prior notice. Appointments assigned to the control arm follow usual practice (same system but no letter attachment). The primary outcome is the proportion of nonattendance. Secondary outcomes are proportions of cancellations, sociodemographics, and health-problem characteristics. Furthermore, the intervention costs and production value of nonattended appointments will be measured. An analysis of effect and cost-effectiveness will be conducted based on a 5 % significance level.

**Discussion:**

The study is initiated and funded by the Danish Regions, which have the responsibility for the Danish public healthcare sector. The results are expected to inform future decisions about the introduction of fines for nonattendance at public hospitals.

**Trial registration:**

Current Controlled Trials, ISRCTN61925912. Registered on 6 July 2015.

## Background

Recent hospital episode statistics from the United Kingdom show that approximately 20 % of scheduled outpatient appointments are nonattended [1]. While hospital and user cancellations each account for almost one third of the nonattended appointments, 7 % of nonattended appointments remain unaccounted for. Seven percent nonattendance is estimated to represent a cost to the healthcare system of around £790 million per year in the United Kingdom [2].

Outpatient nonattendance refers to the phenomenon of users who have an appointment but do not show up at the specified date, time, and location without giving notice. In addition to affecting the efficiency of production and thereby increasing the total costs of care, nonattendance might also delay access to care for users on waiting lists. Moreover, nonattendance has been suggested to have a detrimental effect on health outcomes [3, 4], an effect that is unevenly distributed across disease and socioeconomic groups [5, 6].

Stubbs et al. conducted a systematic literature review to assess the efficacy of various reminder interventions for reducing outpatient nonattendance such as telephone, mail, text/short message service, e-mail reminders, and open-access scheduling [7]. They found that almost all of the assessed interventions moderately reduced nonattendance. However, much of this evidence was based on observational studies, and most studies did not control for socioeconomic status and other relevant factors such as age, sex, waiting time, and health-problem characteristics. The recognition of a need for further high-quality studies has been confirmed by similar systematic reviews [8–10].

Another means for reducing outpatient nonattendance, for which there appears to be only vague empirical evidence, is to penalize nonattendance by a fine. According to neoclassical economic theory, user behavior can be influenced by financial incentives. The introduction of a fine for nonattendance will create a stronger incentive for users to appear at their scheduled appointments [11]. This has been demonstrated in two earlier observational studies where the introduction of fines led to a 14 % reduction and a 54 % reduction in nonattendance [12, 13]. These studies, however, only represent before-and-after scenarios, do not consider the likely influence of exogenous factors, and have limited sample sizes. Furthermore, the external validity is questionable due to the 20-year time lag.

In Denmark, the introduction of fines for nonattendance in hospital outpatient clinics has been debated for years [14]. In 2005, a collaborative agreement between the Danish Regions and the Danish Medical Association opened the opportunity for privately practicing specialists to issue nonattendance fines of Danish kroner (DKK) 250 for consultations and DKK 500 for surgical procedures (1 EUR = 7.45 DKK) [15]. Overall, the expected benefits were related to a better use of resources, whereas concerns were expressed about the detrimental effect on equal access for equal needs, as the fines would impact the most vulnerable users most strongly. Moreover, the use of fines was seen as a break with the fundamental value of free and equal access to healthcare and a potential threat to the patient-health professional relationship, which ideally should be independent of financial interests [14].

Although 10 years have passed since the regulatory context cleared the way for fines in the Danish healthcare system for privately practicing specialists, no systematic evidence on the resulting practice, efficacy, or effect appears to have been reported. Therefore, the Danish Regions have decided that the effect of using fines to moderate nonattendance at somatic, hospital-based, outpatient clinics in Denmark should be scientifically investigated [16]. This trial is a result of that decision and, in accordance, the aim of this trial is to investigate the effect of fines on nonattendance in a hospital-based outpatient clinic. The primary hypothesis is that the risk of fines will incentivize healthcare-service users to attend appointments more often than if no risk of fines is associated with nonattendance of a planned appointment. A secondary hypothesis is that the pattern of attendance will be affected by the risk of fines in terms of who attends (user characteristics) and what type of appointment is being attended (appointment characteristics). The rationale for the second hypothesis is to address the political focus on preserving equal access to healthcare and on variation in provider efficiency. Finally, a third hypothesis is that the use of fines in routine practice will be cost effective.

## Methods/design

A randomized controlled trial (RCT) will be conducted at a hospital-based orthopedic outpatient clinic in the Central Denmark Region. Randomization to an intervention arm (risk of fine) or to a control arm (no risk of fine) will be undertaken at the appointment level, starting in May 2015 and proceeding for 7 months. The trial conduct, analysis, and reporting will be in accordance with the Standard Protocol Items: Recommendations for Interventional Trials (SPIRIT) guidance 2013 [17] and the Consolidated Standards Of Reporting Trials (CONSORT) statement [18].

### Setting

The Department of Orthopedic Surgery at Viborg Regional Hospital consists of an outpatient clinic and a ward. The outpatient clinic has 18,500 scheduled appointments a year, of which approximately 19 % are cancelled and 5 % are nonattended (see Table 1). Medical secretaries manage the booking via an electronic booking system that automatically generates appointment letters that are sent to users. Apart from this system, a substantial number of appointments are scheduled without a sufficient time lag to allow for the dispersal of appointment letters (e.g., in cases of acute health problems) and thus are not considered in the present study.

**Table 1 Tab1:** Historical number of cancelled (% of scheduled) and nonattended (% of noncancelled) appointments from April 2014 to March 2015 for the study setting

		Cancelled appointments			
	Scheduled appointments	By hospital	By user	Total	Nonattended appointments
April 2014	1,473	187 (13)	95 (6)	282 (19)	55 (5)
May 2014	1,467	223 (15)	105 (7)	328 (22)	64 (6)
June 2014	1,869	307 (16)	94 (5)	401 (21)	83 (6)
July 2014	1,082	175 (16)	66 (6)	241 (22)	50 (6)
August 2014	1,562	262 (17)	52 (3)	314 (20)	68 (5)
September 2014	1,661	270 (16)	151 (9)	421 (25)	62 (5)
October 2014	1,634	208 (13)	223 (14)	431 (26)	41 (3)
November 2014	1,744	205 (12)	89 (5)	294 (17)	71 (5)
December 2014	1,583	190 (12)	52 (3)	242 (15)	62 (5)
January 2015	1,511	166 (11)	30 (2)	196 (13)	60 (5)
February 2015	1,387	118 (9)	36 (3)	154 (11)	48 (4)
March 2015	1,520	147 (10)	44 (3)	191 (13)	50 (4)
Total	18,493	2,458 (13)	1,037 (6)	3,495 (19)	714 (5)

Note: All appointments booked by appointment letter are included (not appointments booked by telephone)

Users can call or e-mail to give notice of nonattendance or to have their appointment rescheduled. The secretary is open for telephone calls between 0745 and 1430 on weekdays and can be contacted via e-mail 24 hours a day/7 days a week. A short message service (SMS) reminder system is used to prevent nonattendance; however, this can only be used for follow-up appointments, as the user’s phone number is not available until an initial visit has been attended or if the user has attended the clinic before. Based on historical data, we expect that 20–30 % of scheduled users will continue receiving SMS reminders.

### Participants

Consecutive users scheduled for diagnostics, treatment, surgery, or follow-up in the outpatient clinic by appointment letter sent between 1 May 2015 and 1 December 2015 are included. As a user may have more than one appointment, only the first appointment during this period was considered. Users who were issued more than one appointment letter before the first appointment date were excluded. Appointments booked without an appointment letter (e.g., via telephone or face-to-face) are also excluded from the study. Appointments for physiotherapy or occupational therapy, which are typically group-based and scheduled without appointment letters as well as appointments for users residing in Greenland (requiring an overseas flight) are similarly excluded.

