### Randomization and consent

User-level 1:1 randomization is conducted according to the time of booking using the electronic patient booking system (BookPlan via MidtEPJ). The booking system automatically generates a random number and assigns the appointment to one of the randomization arms. These data are kept from the secretary and other healthcare professionals unless the user informs them (e.g., in the case of questions or complaints). The researchers will be fully blind throughout the trial and data analysis. The study was considered a quality-improvement project, and informed consent from users was not required by The Ministry of Health and Prevention (See Ethics and data protection). However, users were informed of the risk of receiving a fine on nonattendance at this outpatient clinic via the media and via posters and booklets at the hospital. Furthermore, in Denmark, users have free hospital choice.

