### Comparators

All appointments will be made in accordance with the usual practice except for two aspects. First, the appointment letter will inform the user (for both the intervention and control arms) about the trial. The letter will explain that the investigation has been initiated by the Danish Regions and approved by the Ministry of Health and that the patient’s appointment has been randomly assigned to be subject to a fine in the case of nonattendance without notice by the patient if a letter about the fine system is attached to the appointment letter. Second, for appointments randomized to the intervention group only, a letter specifying the conditions for the fine assessment is attached to the appointment letter. This letter clearly indicates that a fine will be issued in the case of nonattendance if the patient does not give notice prior to the time of the appointment. The patients are also informed that the fine amounts to DKK 250 and that it will be issued by a central office under the local government administration (Corporate Finance, Central Denmark Region), which is open for e-mails and telephone calls during normal office hours if the patient has any questions or complaints.

The secretary registers nonattended appointments in the clinic daily. If a user shows up late, the health professionals will usually attempt to see the user anyways. A list of nonattended appointments will be automatically sent once a week to the central office administering the fine system. Similarly, this office will receive the list of included appointments once a week to handle questions and complaints. Fines will be issued once a week, and recipients are given 4 weeks before the fine is due. In the case of nonpayment, users will receive two reminders; thereafter, the collection of the fine will be handed over to the tax authority (SKAT), which will collect the fine and related expenses.

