### Analysis of effectiveness

The principle of intention-to-treat will be used for analysis, and each of the outcome parameters will be compared between the intervention and the control groups. A simple test of proportions will be used to test the primary hypothesis. The secondary hypotheses will be tested in two probit regressions: one for user characteristics and one for appointment type characteristics. Both models will have attendance as the dependent variable and a randomization group dummy and user/appointment type characteristics as covariates along with interaction terms for the randomization group dummy and the covariates. The interpretation of the interaction terms will then be the effect modification of the covariates, which is the same as a differentiated effect of fines on different users/types of appointments. A significance level of 0.05 will be used for all analyses.

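### Excluding users who receive a second letter acts after randomisation, conflicts with the stated intention-to-treat analysis and can truncate the cancellation outcome; the effect on the primary outcome cannot be sized from the article

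*Protocol article*

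**What the plan says.** - **Exclusion** (Participants): "Users who were issued more than one appointment letter before the first appointment date were excluded". The rule has no exception for rescheduling and does not retain such users under their first allocation.
- **Timing of allocation** (Randomization and consent): "User-level 1:1 randomization is conducted according to the time of booking". The Methods/design introduction describes the unit differently: randomisation "will be undertaken at the appointment level".
- **Letters and rescheduling** (Setting): secretaries book through an "electronic booking system that automatically generates appointment letters that are sent to users". "Users can call or e-mail to give notice of nonattendance or to have their appointment rescheduled".
- **Incentive** (Comparators): only the intervention arm receives the attachment, which warns that "a fine will be issued in the case of nonattendance if the patient does not give notice prior to the time of the appointment".
- **Analysis** (Analysis of effectiveness): "The principle of intention-to-treat will be used for analysis".
- **Outcomes**: the Abstract gives nonattendance as the primary outcome and cancellations as a secondary one. Measures of effectiveness words the primary outcome as attendance. Table 1 expresses nonattendance as a percentage of noncancelled appointments.

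**The concern.** Whether a second letter is issued becomes known only after the arm has been assigned and the first letter sent. Users can see their allocation, and the fine rewards giving notice. A rule that removes people with a second letter may therefore select on a response to the intervention, and do so unequally between arms. An analysis that keeps every user as randomised cannot also drop users for this reason.

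Two results are exposed. For cancellations, a user who cancels and is rebooked by letter before the index date leaves both numerator and denominator, so the outcome loses some of the behaviour it is meant to count. For the primary outcome, the analysed arms may no longer be comparable.

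**Working it through.** **1. The plan's own figures.** Inputs from Sample size: 4.8 % vs 3.22 %, 90 % power, 3,250 per arm; alpha 0.05 from Analysis of effectiveness, taken as two-sided.

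n = [1.960·√(2·0.0401·0.9599) + 1.2816·√(0.048·0.952 + 0.0322·0.9678)]² / 0.0158² = 3,239 per arm. Power at 3,250 is 90.1 %. The stated size reproduces.

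From Table 1: nonattended / noncancelled = 714 / (18,493 − 3,495) = 4.76 %, which matches the planning rate of 4.8 %. Nonattended / all scheduled = 714 / 18,493 = 3.86 %. Cancelled by user: 1,037 / 18,493 = 5.6 %. Cancelled by hospital: 2,458 / 18,493 = 13.3 %. Total: 18.9 %.

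**2. Order of events.** Booking → arm assigned → letter → possible second letter → exclusion. The exclusion follows randomisation whatever caused the second letter.

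**3. Nonattendance, user cancellations only.** Assumptions: every user cancellation (5.6 %) is rebooked by letter before the index date and excluded; the fine moves 1.28 % of randomised users from no-show to rescheduling. The 1.28 % is the design effect per randomised user: 1.58 × (1 − 0.189) = 1.28. Per arm of 3,250: 125.5 no-shows in control, 41.6 converts in the fine arm, 182 excluded in control.

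| Analysis | Control | Fine | Difference |
|---|---|---|---|
| All randomised | 125.5/3,250 = 3.86 % | 83.9/3,250 = 2.58 % | 1.28 points |
| After exclusion | 125.5/3,068 = 4.09 % | 83.9/3,026 = 2.77 % | 1.32 points |

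The inflation is 1.32/1.28, about 3 %.

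**4. Other assumptions about who rebooks.** Take 5.6 % excluded and 4.8 % nonattending among those analysed in control, so no-shows are 0.048 × 0.944 = 4.53 % of randomised users.
- Extra exclusions x in the fine arm, all would-be nonattenders: the analysed rate is (0.0453 − x)/(0.944 − x). For x = 0.5, 1.0 and 1.58 points, the analysed reductions are 0.51, 1.02 and 1.62 points. The reductions per randomised user are 0.50, 1.00 and 1.58, so the excess is 1 to 3 %.
- Extra exclusions all would-be attenders: the rate is 0.0453/(0.944 − x). For x = 1 to 5 points it rises to 4.85 % to 5.07 %, a shift of 0.05 to 0.27 points against the fine. The upper end needs user rebooking nearly to double in one arm.

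**5. Cancellations.** In the step 3 scenario, user cancellations are 5.6 % vs 5.6 + 1.28 = 6.9 % of randomised users, a difference of 1.28 points. If none are rebooked by letter, that difference is seen in full. If all are, every one of these users is excluded and the observed difference is zero.

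**The case against.** **The trigger is inferred.** No section says that rescheduling issues a new letter. Users reschedule by telephone or e-mail, and Participants treats telephone bookings as made without a letter. Some or most rescheduling may never meet the rule. This stands, and it limits confidence in any arm difference.

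**Much rebooking should balance.** Of the 18.9 points of cancellations, 13.3 are by the hospital. Those are not a response to a fine, and allocation is kept from the secretary. This also stands.

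**A reader might infer a large overstatement of the effect.** If all 18.9 % are excluded, the step 3 contrast becomes 125.5/2,636 − 83.9/2,594 = 4.76 % − 3.23 % = 1.53 points, apparently 19 % above 1.28. That gap reflects a change from all scheduled to noncancelled appointments. Keeping everyone, counting the converts as cancelled and using Table 1's noncancelled denominator also gives 4.76 % vs 3.23 %. Excluding an equal 614 per arm gives 1.58 points, so the extra exclusions in the fine arm lower the contrast. The risk ratio barely moves: 0.668 for all randomised, 0.679 after exclusion.

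**A reader might also infer that the exclusion could manufacture the 1.58-point design effect.** The 1.62-point reduction in step 4 is a real fall of 1.58 points in no-shows at the index appointment. Users who give notice are not nonattenders under any analysis.

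**The rule may guard against contamination.** It could be meant to remove users holding letters from both arms, although the article gives no purpose. That would be a legitimate aim, but exclusion replaces dilution with possible selection of unknown direction.

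**Conclusion.** The conflict is established by the text: the exclusion acts after randomisation, intention-to-treat is claimed, and nothing in the article reconciles them. Truncation of the cancellation outcome follows if rebooking generates letters.

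Material bias in the primary outcome is not shown. With user cancellations only, the inflation is about 3 % (1.32 vs 1.28 points), measured against all randomised users. On a noncancelled denominator, excluding users whose index appointment was cancelled changes nothing, but that denominator itself conditions on cancellation after allocation. The direction depends on who rebooks.

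A power loss might also be inferred. Removing 5.6 % to 18.9 % from 3,250 per arm would lower power from 90.1 % to between 88.4 % and 83.2 %. However, the 6,500 are described as eligible appointments and may already be net of exclusions, so this is not established either.

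This should be fixed, at moderate confidence.

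**What to change.** - In the primary analysis, keep every randomised user in the arm of the first letter in the inclusion window, whatever letters follow.
- Classify that index appointment as attended, cancelled or nonattended, and state one denominator used for both arms. All randomised users is the choice that fits intention-to-treat; a noncancelled rate can be reported beside it.
- Move the single-letter subset to a sensitivity analysis, and report the number with a second letter by arm and, where recorded, by who initiated the rebooking.
- State whether a rebooked appointment issues a new letter and a new allocation, and reconcile the user-level and appointment-level descriptions of randomisation.

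**Cost.** This changes the analysis set and its wording; allocations and bookings come from the electronic booking system. The downside is dilution. If each booking was allocated anew at 1:1, up to about half of two-letter users may hold letters from both arms: 0.5 × 5.6 = 2.8 % of users if only user cancellations are rebooked by letter, and 0.5 × 18.9 = about 9 % if all cancellations are. The sensitivity analysis would show whether this matters.

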### Randomization and consent

User-level 1:1 randomization is conducted according to the time of booking using the electronic patient booking system (BookPlan via MidtEPJ). The booking system automatically generates a random number and assigns the appointment to one of the randomization arms. These data are kept from the secretary and other healthcare professionals unless the user informs them (e.g., in the case of questions or complaints). The researchers will be fully blind throughout the trial and data analysis. The study was considered a quality-improvement project, and informed consent from users was not required by The Ministry of Health and Prevention (See Ethics and data protection). However, users were informed of the risk of receiving a fine on nonattendance at this outpatient clinic via the media and via posters and booklets at the hospital. Furthermore, in Denmark, users have free hospital choice.

### Sample size

Based on department statistics, a nonattendance rate of 4.8 % and a volume of 6,500 eligible appointments during a time window of 7 months are assumed. This time window was adopted to balance of arguments concerning effect size and stability in the study, which are exerted for restructuring and cost cutting after the 7 months. A minimum reduction of 1.58 % (from 4.8 % to 3.22 %) was found using a chi-squared test and a 90 % power level. The randomization ratio is 1:1, which indicates that 3,250 users are required in each arm. The power to detect similar impacts on the secondary outcome parameters of cancellations will be higher due to higher baseline proportions. The power to detect the impact on sociodemographics will depend on the scaling and the relevant level of relative risk reduction [19].

